### Economic analyses

The economic analysis will be conducted from both a health sytem perspective, and from a broader perspctive including productivity impacts in order to determine the difference in costs and outcomes in Group PM+/E-CAU, compared with E-CAU. Costs will be compared between arms using a regression model, controlling for baseline, and with bootstrapped confidence intervals using 10,000 resamples. Incremental cost-effectiveness ratios (ICERs) will be calculated comparing changes in mean costs and primary outcomes from both payer and societal perspectives between the two groups. Non-parametric bootstrapping analyses, using 10,000 resamples, will be performed to account for uncertainty and derive 95% confidence intervals around ICERs in order to generate cost-effectiveness planes. Cost-effectiveness acceptability curves will be plotted to present the probability that the PM+/E-CAU intervention is cost-effective at various willingness-to-pay threshold levels.

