#### Sample size and power calculations

The Vrije University (VU) University Medical Centre Department of Epidemiology and Biostatistics carried out the power calculations for this study. Considering previous studies with PM+ in Peshawar, Pakistan, and Nairobi, Kenya, we aim for a conservatively estimated small to medium Cohen’s d effect size of 0.4 in the PM+ group at the 3-month follow-up [13, 15]. Power calculations suggest a minimum sample size of 133 participants per group (power = 0.90, a = 0.05, two-sided). Considering an expected 30% attrition at the 3-month follow-up, we aim to include a total number of 380 participants (190 in the Group PM+/E-CAU group and 190 in the E-CAU group).

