#### Randomization

After baseline assessment, participants will be randomly assigned on a 1:1 basis to either Group PM+/E-CAU (*n* = 190) or E-CAU (*n* = 190) (T0). Randomization using computerized software will be carried out by an independent researcher who is not involved in the intervention delivery, clinical supervision, assessments or other aspects of the study.

There is a chance that participants of the study will be recruited from the same household, creating a risk for contamination (if family members were to be allocated to receive different treatments, namely either Group PM+ or E-CAU). To limit the likelihood of contamination, participants from the same household will be assigned to the same intervention arm.

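### The bootstrap interval around the ICER cannot be interpreted if the HSCL-25 estimate falls below about d = 0.24, and the cost-effectiveness plane does not need it

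*Protocol article*

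**What the plan says.** In the protocol article, Economic analyses, the ICERs are to be "calculated comparing changes in mean costs and primary outcomes from both payer and societal perspectives between the two groups". The denominator is therefore the between-arm difference in the primary outcome, the HSCL-25. Non-parametric bootstrapping with 10,000 resamples is then used to "derive 95% confidence intervals around ICERs in order to generate cost-effectiveness planes". The next sentence adds a second display: "Cost-effectiveness acceptability curves will be plotted to present the probability that the PM+/E-CAU intervention is cost-effective at various willingness-to-pay threshold levels". The section gives no rule for the ICER interval when the bootstrapped effect differences fall on both sides of zero.

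The precision of the denominator follows from Sample size and power calculations. The trial is planned for a Cohen's "d effect size of 0.4 in the PM+ group at the 3-month follow-up", with "power = 0.90, a = 0.05, two-sided". That section continues: "Power calculations suggest a minimum sample size of 133 participants per group".

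**The concern.** Two things in the planned sentence look wrong.

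First, the order of derivation is reversed. A cost-effectiveness plane shows one point per replicate, with the effect difference on one axis and the cost difference on the other. It comes directly from the resamples, and an interval for the ratio plays no part in it.

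Second, a ratio loses its ordering when its denominator can be zero or change sign. Count a fall in HSCL-25 as a gain. A replicate that is cheaper and better gives a negative ratio, and so does one that is dearer and worse. Near a zero effect difference the ratio runs off to plus infinity on one side and minus infinity on the other. Sorting the ratios and reading off limits then mixes the best and the worst results.

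Cost-effectiveness is part of the main objective (Objectives), and the abstract ties release of the manual to its being established. The health-system and the broader ICER share the same denominator, so both intervals would fail together.

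**Working it through.** **Inputs from the protocol article.** d = 0.4; power 0.90; two-sided alpha 0.05; 133 per arm; 30% attrition; 380 in total (Sample size and power calculations); 1:1 allocation (Randomization).

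**The plan's own figure.** Normal approximation: n = 2(1.96 + 1.2816)² / 0.4² = 131.3, rounded up to 132. The two-sample t-test gives 132.3, rounded up to 133. Attrition: 133 / 0.70 = 190 per arm, 380 in total. The stated sample size reproduces.

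**When the interval fails.** On the standardised scale, the effect difference has SE = sqrt(2/n) = sqrt(2/133) = 0.1226. If the estimate is d, the share of replicates on the wrong side of zero is Phi(−d/SE):

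- d = 0.40: 0.06%
- d = 0.30: 0.7%
- d = 0.20: 5.1%
- d = 0.15: 11%
- d = 0.10: 21%

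A limit of a 95% percentile interval falls among the wrong-side replicates once their share exceeds 2.5%, that is, when the estimate is below 1.96 × 0.1226 = 0.24. In this approximation that is the same condition as a primary-outcome estimate in the favourable direction missing two-sided p < 0.05, or an estimate in the wrong direction.

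**How often.** For a true effect d, the chance of an estimate below that threshold is Phi(1.96 − d/SE):

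| True d | 133 per arm | 190 per arm (no attrition) |
|---|---|---|
| 0.40 | 10% | 3% |
| 0.35 | 19% | 7% |
| 0.30 | 31% | 17% |
| 0.24 | 50% | 35% |
| 0.20 | 63% | 50% |
| 0.10 | 87% | 84% |

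Worked line: at d = 0.30, d/SE = 2.45, and Phi(1.96 − 2.45) = 0.31.

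**What the reader would see.** The article gives no cost figures, so the following is an illustration under assumptions: an estimated d of 0.15, an incremental cost of 0.3 cost-SDs, and cost and effect uncorrelated. The ICER is 0.3 / 0.15 = 2.0 (cost-SDs per outcome-SD). In a normal-approximation simulation with 133 per arm the percentile interval runs from about −16 to +20. About 11% of replicates are dearer and worse and only about 0.6% are cheaper and better. A negative lower limit looks like a possible saving, but it comes almost entirely from the opposite quadrant.

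**Coverage.** Trials were simulated with incremental costs of 0.1, 0.3 and 0.5 SD and true d from 0.1 to 0.4. Where more than 2.5% of replicates crossed zero, the lower limit was negative in essentially all trials, and the interval contained the true ICER in 99–100% of them. So in those trials the interval is wide and unreadable; it does not under-cover.

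**The case against.** The strongest reply is that the same section already plans the plane and the acceptability curve. Both use the joint replicates and stay interpretable when the effect is uncertain. That stands, and it limits the harm to one economic summary. A reader might infer that the trial could not tell a cheaper-and-better result from a dearer-and-worse one. The documents do not support that, because the plane shows the quadrants.

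A second reply is that the article does not name percentile limits, and that a condensed article may leave the construction of the interval to a fuller document. This stands in part: the percentile reading used above is an assumption. The commitment to an interval around the ratio is stated, however, and so is the claim that it serves to generate the plane. Any single ordered range of ratios meets the same difficulty when the denominator straddles zero.

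Third, a reader might infer that the interval is likely to fail whenever the effect is below plan. The arithmetic does not support that: at a true d of 0.30 to 0.35 the chance is 19–31%. A reader might also infer under-coverage in the trials where replicates cross zero, which the simulation does not show, or that clustering makes matters worse. The article gives no intracluster correlation, and the baseline covariate in the primary model works in the other direction, so the net effect cannot be stated.

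**Conclusion.** The point holds as a limited improvement. The stated purpose of the ICER interval is mistaken, since the plane does not depend on it. The interval becomes uninterpretable when the estimated d is below about 0.24 with 133 per arm, or about 0.20 with 190. The chance is about 10% at the planned effect. It passes one half only when the true d is under about 0.24, a shortfall of about 40% from plan. At an estimate equal to the planned effect, with 0.06% of replicates crossing, the interval is not seriously affected.

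These figures assume a normal approximation, an unadjusted comparison at the 3-month follow-up and percentile limits. They ignore the precision gained by baseline adjustment and the precision lost through shared households and treatment groups, because the article quantifies neither. The primary analysis, the plane and the acceptability curve are unaffected.

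**What to change.** Reword the sentence in Economic analyses to say four things:

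- The plane and the acceptability curve are built from the joint bootstrap replicates of cost and effect differences.
- Uncertainty is summarised as incremental net monetary benefit with a 95% bootstrap interval, over the same willingness-to-pay range as the acceptability curve.
- An ICER interval is reported only when the replicates of the effect difference lie clearly on one side of zero, by a criterion fixed in advance (for example, fewer than 2.5% crossing).
- Otherwise the ICER is given as a point estimate beside the plane.

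Dropping the ICER interval in every case would go further than needed, since it is serviceable when the effect is clear. The change uses the 10,000 resamples already planned. It needs no further data and no change to sample size, and costs only the rewording.

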### Ethical considerations

The study protocol received approval from the ISU Research Ethics Committee on 12 April 2017 (Protocol ID: 12/2017) and the Immigration Authority of the Republic of Turkey to conduct the study on 29 March 2017. The STRENGTHS Safety Board (SB) will ensure that the trial and data collection are conducted in accordance with the principles of the Declaration of Helsinki (64th WMA General Assembly, Fortaleza, Brazil, October 2013). It will be in accordance with the International Conference on Harmonisation, WHO Good Clinical Practice standards, and the Medical Research Involving Human Subjects Act (WMO). There is no anticipated harm or compensation for trial participation. Cases of clinical worsening will be referred to tertiary care.

#### Trial management

The trial management committee consists of the site principal investigator (PI) and research coordinators, who are responsible for monitoring of all study procedures. Overall trial management is provided by the international PI and senior research and intervention staff, who hold monthly telephone conferences and meet annually in a face-to-face consortium meeting. The STRENGTHS SB will monitor all ethical, legal and societal issues that arise within the STRENGTHS project. In addition, the safety, rights and wellbeing of study participants and research staff will be reviewed, and interim analyses will be considered in case safety issues are (suspected to be) violated. Relevant issues will be discussed periodically (on a 6-month basis); the SB will request that additional meetings be held if issues arise in the interim.

Moreover, any amendments to the protocol will be made after a favourable opinion of the consortium and the ISU Research Ethics Committee. The coordinator of the project will then notify the funder and will update the protocol in the clinical trial registry. Any deviations from the protocol will be fully documented by using a breach report form*.*

#### Adverse event monitoring

All adverse events (AEs) and serious adverse events (SAEs) will be recorded through the web-based software, Castor Electronic Data Capture. SAEs will be reported to the ISU Research Ethics Committee within 15 days. SAEs that result in death or are life-threatening will be reported within 48 hours. All AEs will be followed until they have abated or until a stable situation has been reached.

## Discussion

This study reports the protocol of an RCT that evaluates the effectiveness and cost-effectiveness of the culturally adapted version of Group PM+ among adult Syrians residing in Turkey. PM+ is a five-session-long, trans-diagnostic psychological intervention developed by the WHO and aims to decrease symptoms of psychological distress (depression, anxiety and PTSD) and to improve psychosocial functioning.

This study builds on prior research that has demonstrated the effectiveness of PM+ in different settings in decreasing depression and anxiety symptoms [13, 15, 16]. However, PM+ has not been adapted for Syrian refugees who migrated to Europe and the Middle East after experiencing adversities in Syria, during and after migration. We hypothesise that training Arabic speakers in Group PM+ and providing peer-to-peer Group PM+ to refugees may be useful in overcoming the mental health treatment gap we are seeing in this population group. If proven to be effective, the adapted Group PM+ version will be disseminated by the WHO and recommended for scaling up.

## Trial status

The trial was registered at ClinicalTrials.gov on 21 May 2019 (ClinicalTrials.gov Identifier: NCT03960892, protocol version 4.2/201903). Recruitment of participants began on 3 August 2019 and we are planning to finish it in June 2020.

## Data Availability

The datasets analysed during this study are available from [name], Koc University, Istanbul, Turkey, on reasonable request.

## Abbreviations

AE: Adverse event
CSRI: Client Service Receipt Inventory
E-CAU: Enhanced care as usual
E-TAU: Enhanced treatment as usual
IC: Informed consent ICER Cost-effectiveness ratio
ISU: Istanbul Sehir University
ITT: Intention to treat
PCL-5: PTSD Checklist for DSM-5
PI: Principal investigator
PM+: Problem Management Plus
PMLDC: Post-Migration Living Difficulties Checklist
PSYCHLOPS: Psychological Outcomes Profiles
PTSD: Post-traumatic stress disorder
RASASA: Refugee and Asylum Seekers Assistance and Solidarity Association
RCT: Randomized controlled trial
SAE: Serious adverse event
SB: Safety Board
SPIRIT: Standard Protocol Items: Recommendations for Clinical Interventional Trials
STRENGTHS: Syrian Refugees Mental Health Care Systems
WHO: World Health Organization
WHODAS: World Health Organization Disability Assessment Schedule
